### Study intervention

Our intervention will be coordinated with a large general hospital, community hospitals and participants' families to provide integrated and continuous management to T2DM patients through the diabetes management system. Our intervention focuses on improving patient glycemic control and all essential aspects of self-management (blood glucose measurement, diet, exercise, medication adherence and diabetes-related knowledge). The i-HCH program intervention (Fig. 2) is designed to address the discontinuation of information and management between hospital and community care and enhance the role of family caregivers. The transitional care team will use the app to work directly with participants. Before the intervention, the team will undergo five days of training in the i-HCH program and app. The training aims to ensure that the care team has knowledge and interest in using the app to manage in-home participants in the long term. After the five days of training, the community team will continue to be trained every month on up-to-date clinical guidelines on diabetes knowledge and how to improve participants' self-management skills. CNs can consult with and refer to transitional care team members to obtain support to resolve the gap in care during the intervention.

**Fig. 2 Fig2:**
[figure not shown]
Summary of key components and features of the i-HCH program intervention for T2DM patients

Clinical nurses will be responsible for assessing individual symptoms, signs, and self-care behavior to make personalized discharge plans, including the patients' recent medical history, medication list, measurement frequency of blood glucose, and therapeutic target three days before discharge. Clinical nurses will encourage patients to select a family member who is willing and able to provide diabetes care at home and will install and demonstrate the app on participants' and family members' smartphones, giving them the motivation and skill to use the app. The clinical nurses will ensure that patients and their families are ready to be discharged and will share the discharge plan with them and the transitional care team.

CNs will remotely monitor the patients' health records at patient discharge through the app, including blood glucose, blood pressure, BMI, medication adherence, nutrition, physical activity, and emotion. The app will automatically provide alerts for abnormal indicator values and send texts on measurement target recommendations in real-time. CNs will implement individual interventions based on the risk stratification of patients by the app. They will use the app to send interactive messages once a month to patients, including messages setting evidence-based glycemic measurement goals, encouraging healthy behaviors and guiding family members to provide more additional assistance to in-home patients. CNs will identify the causes of poor blood glucose management in warning and key patients using the app counseling function and send tailor-made health recommendations. CNs will use the app to support and encourage patients to communicate with team members remotely. If the patient asks for a disease-related consultation, the CN or GP should handle it within 24 h. Patients have the option of refusing to accept the above information. Subsequently, CNs will continue to supervise the patient's blood glucose value and, if necessary, call or see the patient in their home.

Team members will transmit educational articles on the app weekly to patients and their families to help them learn about diabetes, such as hypoglycemia and signs of exacerbation. The pharmacist will provide professional pharmaceutical knowledge, such as skills on taking medication correctly, the importance of medication adherence and ways to adjust the insulin dose.

CNs will note app usage and self-care status and present health information for discussion in monthly team meetings. The intervention strategy will be adjusted accordingly to meet patients' needs when member consensus is achieved. Then, routine endocrinologist appointments will be performed in the third and sixth months after discharge. The app will send follow-up reminders to patients and provide information on the critical content and a preparation list two weeks before follow-up. Patients will be immediately recommended to schedule urgent appointments and will be referred to the general hospital with the responsible endocrinologist if they have unsafe glycemic levels or develop acute or chronic diabetic complications.

In the control group, participants will receive usual transitional care alone. Participants who achieve stable blood glucose are usually discharged with an in-home management plan drawn up by clinical nurses and physicians. Outpatients will attend regular clinic visits at the general hospital, with an interval of approximately three months. Participants can access health care from community hospitals in-between clinic visits if needed. The clinical nurses will perform a consultation to assess the outpatient's self-management condition once every three months and obtain blood glucose data that patients provide via a paper record or from a commercial glucose meter over the telephone or during a home visit; in addition, the clinical nurses will provide general advice and renew the diabetes management plan.

### Sample size

Our sample size estimation was performed using R Studio software based on HbA_1c_. A total of 126 participants from an endocrinologist in the general hospital are required to detect a mean difference in HbA_1c_ of 0.5% over six months between the intervention and control groups with a standard deviation of 1 to achieve 0.8 power and a two-sided alpha of 0.05. Allowing for a 10% attrition rate, the total participant number should be 138, or with 69 participants in each group.

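### The stated total of 138 does not keep the required 126 participants after the stated 10% attrition: about 124 remain, a minor inconsistency that 140 would remove

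*Protocol article*

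**What the plan says.** The Sample size section of the protocol article bases the calculation on HbA1c. It states the requirement as "A total of 126 participants from an endocrinologist in the general hospital are required". The purpose is given as "to detect a mean difference in HbA_1c_ of 0.5% over six months between the intervention and control groups". The assumed SD is 1, the power 0.8 and the two-sided significance level 0.05. The enrolment target comes in the sentence after that: "Allowing for a 10% attrition rate, the total participant number should be 138, or with 69 participants in each group".

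The Study design section fixes 1:1 allocation, so 126 means 63 per group. The section gives neither the formula used to inflate for attrition nor the rounding rule. The Statistical analysis section plans an intention-to-treat analysis in which missing data are imputed. It does not name the imputation method.

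**The concern.** An attrition allowance exists so that the required number remains after the assumed loss. The section prints all three elements: a requirement (126), a loss rate (10%) and an enrolment total (138). Anyone can therefore check whether the third follows from the first two, and it does not.

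This is the number the trial will recruit to and report as its planned size. If it is short, the stated power no longer corresponds exactly to the stated attrition, and a reader who checks the sum will find the mismatch. How much that matters depends on the size of the shortfall, worked out below.

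**Working it through.** **Inputs**, from the Sample size section unless noted:
- difference 0.5, SD 1
- "a two-sided alpha of 0.05", power 0.8
- attrition 10%
- required total 126, enrolled total 138 (69 per group)
- allocation 1:1 (Study design)

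**1. Reproduce 126.** By the normal approximation for two means:

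n per group = 2 × (1.960 + 0.842)² × 1² / 0.5² = 62.79, rounded up to 63, so 126 in total.

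This matches exactly, so 126 is right for the stated inputs under that method.

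**2. Apply the stated loss to the stated total.**
- 138 × 0.9 = 124.2 in total; 69 × 0.9 = 62.1 per group.
- In whole participants that is about 124, or 62 per group, against 126 and 63. The shortfall is 2.

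**3. Find the total that keeps 126.**
- 126 / (1 − 0.10) = 140, or 70 per group.
- Check: 70 × 0.9 = 63.

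**4. Find the loss that 138 can absorb.**
- 138 − 126 = 12, and 12/138 = 8.7%.

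**5. Where 138 may come from.**
- 126 × 1.1 = 138.6.
- From the unrounded requirement, 62.79 × 1.1 = 69.07 per group, or 138.1 in total.
- Both lie close to 138, so multiplication by 1.1 is a plausible source. It remains an inference.

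**6. Effect on power**, with difference 0.5, SD 1 and two-sided alpha 0.05, if only completers carry information. Normal approximation: power = Φ(0.5 × √(n/2) − 1.960).
- n = 63: 0.5 × √31.5 = 2.806; Φ(0.846) = 0.801.
- n = 62: 0.5 × √31 = 2.784; Φ(0.824) = 0.795.

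| Per group | Normal approximation | Two-sample t-test (noncentral t) |
|---|---|---|
| 62 | 0.795 | 0.789 |
| 63 | 0.801 | 0.795 |

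Going from 63 to 62 per group costs about 0.6 percentage points of power by either method.

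**The case against.** The best defence is that the gap is trivial. An SD of 1 and an attrition of 10% are round planning values, and 2 participants or 0.6 points of power lie well inside their uncertainty. This stands, and it is why the point is minor. It does not make the three printed figures agree.

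A second defence is that inflating by 1.1 is a common shortcut and that the text does not say what the 10% is a share of. An attrition rate is ordinarily a share of those enrolled, and on that reading 138 falls short. Taken instead as a share of the required 126, 10% is 12.6 and the total is 138.6, so 138 is close but does not follow without a further choice about rounding.

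A third defence is that the plan imputes missing data, so a completers-only calculation is not the planned analysis. This is fair as a limit on the power figures, which are conditional on that assumption. It does not affect the count. The plan itself makes an attrition allowance, and imputation does not generally restore all the information in outcomes that were never observed.

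A reader might also infer more than the document supports:
- **That 138.6 was rounded down.** No formula or rounding rule is given, and the unrounded requirement times 1.1 gives 138.1, which becomes 138 by ordinary rounding.
- **That 126 is itself wrong because a t-test is named for continuous data.** It is a correct normal-approximation result. The t-test power at 63 per group is already 0.795, so that part of the gap reflects the choice of formula and not the attrition step. The Statistical analysis section also assigns the change over time in the primary outcome to repeated-measures ANOVA, so 0.789 is not the power of every planned HbA1c analysis.

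**Conclusion.** The enrolment figure is wrong as written, in a minor way. On the plan's own numbers, 10% attrition from 138 leaves about 124 participants (62 per group), 2 fewer than the 126 stated as required. The total that matches is 140. This part uses only the printed figures and the ordinary meaning of attrition as a share of those enrolled.

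A reader might infer that the trial fails to deliver its 0.8 power. The document does not support that. By the method that reproduces 126, power moves from 0.801 to 0.795. The t-test value at 62 per group is 0.789. All of these are 0.8 to one decimal, the precision at which the article states it. They assume equal groups, the stated difference and SD, and no information from participants who are lost. The finding is an inconsistency in a planning figure and not a material power deficit.

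**What to change.** Change one sentence in the Sample size section, in either of two ways:

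- **Correct the total** to 140 (70 per group), stating that 126/0.9 = 140. The cost is two more participants.
- **Keep 138 and restate what it provides**, for example: *138 enrolled (69 per group) allows for about 8.7% attrition; at 10% attrition about 124 remain, with power about 0.79.* The cost is a stated power about one point lower. The sentence should name the method behind the power figure (0.795 normal approximation, 0.789 two-sample t-test) and say that it counts completers only.

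Either way, giving the inflation formula in the same sentence lets a reader reproduce the total. Nothing else in the design or analysis needs to change for this point.

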### Statistical analysis

Data will be imported into SPSS 23.0 for further statistical analysis. Descriptive statistics, including the mean, standard deviation, and frequency, will summarize all participants' various factors. In order to determine whether the data met the planned statistical analysis hypothesis, the data were examined for distribution and collinearity before the analysis. The analysis will be based on an intention-to-treat (ITT), meaning that all eligible patient information was included in the analysis regardless of whether the intervention was completed. In the primary analysis, Student's t-tests or Mann–Whitney U tests will compare the differences in demographic and diabetes-related information in the two study groups at baseline and endpoint for continuous data or χ2 tests for proportions. The differential changes in repeated measurement data between groups will be assessed by repeated-measures ANOVA and the interaction effect (group × time) across three time points (baseline, three months, six months), aiming to evaluate the impact of the intervention over time on the primary study outcomes. The ITT analyses will also be used to impute missing study data. The analysis of secondary outcomes will be compared similarly to the primary analysis, except for the results of HbA_1c_ levels, where the remaining metrics will not be considered for repeated measurements based on the fact that they were measured ≤ 2 times. A p-value of less than 0.5 will be considered statistically significant.

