We designed a mHealth-based transitional care intervention that creates a support network with multiple agencies to establish a communication bridge between hospitals, communities and home healthcare providers. A professional diabetes-related app was developed to support a transitional care team providing continuous and remote health services for discharged patients. This paper describes the intervention protocol of a multicenter pragmatic randomized controlled trial (RCT) and hypothesizes that it will promote T2DM patients' glycemic control, self-management skills and other health outcomes. Our primary outcome is the change in glycated hemoglobin (HbA_1c_) at the 6-month follow-up; other outcomes are described below.

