### Study outcomes

The change in HbA_1c_ is the primary outcome. The secondary outcome measures are as follows: (1) clinical outcomes, including blood pressure, lipids (total cholesterol [TC], triglycerides [TGs], low-density lipoprotein [LDL], high-density lipoprotein [HDL]), and body mass index (BMI); (2) diabetes self-management skills assessed using the Summary of Diabetes Self-care Activities questionnaire (SDSCA) [34]; (3) quality of life using the Diabetes-Specific Quality of Life scale (DSQL) [35]; (4) diabetes knowledge using the Diabetes Knowledge Test (DKT) [36]; (5) transitional care satisfaction; and (6) the rate of readmission.

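### The HbA1c analysis is not tied to the 6-month change that defines the primary outcome: the deciding test is unclear, the interaction is not specific to 6 months, and baseline HbA1c is not a covariate

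*Protocol article*

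**What the plan says.** - **Outcome.** The Background section gives a time point: "Our primary outcome is the change in glycated hemoglobin (HbA_1c_) at the 6-month follow-up". The Study outcomes section repeats the outcome without one: "The change in HbA_1c_ is the primary outcome".
- **First analysis.** Under Statistical analysis, the tests labelled primary are Student's t or Mann–Whitney, which "will compare the differences in demographic and diabetes-related information in the two study groups at baseline and endpoint". The choice between the two tests follows an inspection of the data's distribution.
- **Second analysis.** The same section continues: "The differential changes in repeated measurement data between groups will be assessed by repeated-measures ANOVA". It specifies "repeated-measures ANOVA and the interaction effect (group × time) across three time points (baseline, three months, six months") and directs this at the primary study outcomes. It adds that outcomes other than HbA1c will not be treated as repeated measurements.
- **Sample size.** The trial is sized on one between-group mean difference in HbA1c of 0.5% over six months, with SD 1, power 0.8 and two-sided alpha 0.05. This gives 126 participants, raised to 138 for 10% attrition.

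No sentence names a 6-month contrast within the ANOVA, a between-group test of the change from baseline to 6 months, or a baseline covariate.

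**The concern.** The outcome and the sample size point to one quantity, the between-group difference in HbA1c at 6 months. The analysis text offers two tests, and neither is clearly fixed to that quantity as the deciding result.

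- The group-by-time interaction over three visits has 2 degrees of freedom. It rejects for any pattern of differential change, including one seen at month 3 and gone by month 6. By itself it is an F test and not an estimate of the 6-month difference.
- The endpoint comparison is at the right time but leaves out baseline HbA1c, which is measured in every patient. If it becomes a Mann–Whitney test, it no longer estimates the mean difference on which the trial was sized.
- The phrase about the primary analysis is attached to the t-test/Mann–Whitney sentence, while the reference to the primary outcomes is attached to the ANOVA. If the two disagree, the text does not clearly say which one is the trial's result.

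**Working it through.** **Inputs from the protocol.** Difference 0.5, SD 1, two-sided alpha 0.05, power 0.8, 126 evaluable, 138 recruited with 10% attrition (Sample size); 1:1 allocation (Study design); visits at baseline, 3 and 6 months (Data collection).

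**Assumptions, not in the protocol.** SD 1 is the SD of HbA1c values at each visit; the protocol does not say whether it is that or the SD of change. The correlation r between any two visits is equal and lies between 0.3 and 0.7.

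**1. The plan's own figure.** n per arm = 2(1.960 + 0.842)² × 1² / 0.5² = 62.8, so 63 per arm and 126 in total. The figure reproduces. After 10% attrition, 138 × 0.9 / 2 ≈ 62 per arm, which is used below.

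**2. Power at 6 months, true effect 0.5.**
- Endpoint t-test: SE = √(2/62) = 0.180, power 79% at every r.
- Baseline-adjusted ANCOVA: residual SD = √(1 − r²) = 0.954/0.866/0.714, standardised effect 0.524/0.577/0.700, power 82%/89%/97%.

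**3. The 2-df interaction.** With equal correlation, the noncentrality is λ = (62/2) × Σ(δₜ − δ̄)² / (1 − r), where δₜ is the group difference at each visit. Power comes from the noncentral F with 2 and 244 df.

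| Effect at baseline, month 3, month 6 | Σ(δₜ − δ̄)² | λ at r = 0.3/0.5/0.7 | Interaction significant |
|---|---|---|---|
| 0, 0.5, 0 | 0.1667 | 7.4/10.3/17.2 | 67%/82%/97% |
| 0, 0.25, 0 | 0.0417 | 1.8/2.6/4.3 | 21%/28%/44% |
| 0, 0.25, 0.5 | 0.1250 | 5.5/7.8/12.9 | 54%/70%/90% |
| 0, 0.5, 0.5 | 0.1667 | 7.4/10.3/17.2 | 67%/82%/97% |

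The first and last rows are identical: under these assumptions the test is as likely to reject for an effect that has vanished by month 6 as for one sustained to month 6. In the first two rows, a test of the 6-month difference rejects in 5% of trials.

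**4. No effect at any visit.** If a significant result on either test were accepted, simulation gives at least one p < 0.05 in about 9% of trials. Two independent tests would give 1 − 0.95² = 9.75%.

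**5. Chance baseline imbalance.** With a 0.2-point imbalance and r = 0.5, the endpoint difference shifts by 0.5 × 0.2 = 0.10 and the simple change score by (0.5 − 1) × 0.2 = −0.10. ANCOVA removes both.

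**6. The other reading of SD 1.** If it is the SD of change, the endpoint SD is 1/√(2(1 − r)) = 0.845/1.000/1.291. At 63 per arm (normal approximation), endpoint power is 91%/80%/59% and ANCOVA power 94%/90%/86%. The ordering is unchanged.

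**The case against.** A reader might infer that the planned analyses do not test the primary outcome at all. The documents do not support that. Under randomisation the expected baseline difference is zero, so the endpoint t-test targets the same mean effect as the 6-month change. The ANOVA has baseline as one of its time points, so its interaction is a joint test of change at 3 and 6 months. It is also wrong to say that baseline HbA1c is discarded, since the ANOVA uses it as a level of time. What is absent is its use as a covariate.

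A reader might also infer two chances at the primary claim. The text never says that either test may decide. There is a reasonable reading in which the ANOVA is the HbA1c analysis: the t-test sentence does not name HbA1c, and repeated measures are reserved for HbA1c. On that reading the 9–10% null rate does not arise, but the deciding test is then the interaction, which is the one not specific to 6 months.

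The size of the problem depends on the pattern of effect. The intervention runs throughout follow-up, so a full effect at month 3 with none at month 6 is an extreme case; a transient 0.25% effect gives much lower figures. With a sustained 0.5% effect and r = 0.7, interaction and ANCOVA power are both 97%.

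Finally, covariance structure and reporting detail can be left to an analysis plan. That is fair, and their absence is no part of this point. The protocol does, however, state a primary analysis, and a later plan would have to override that wording.

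**Conclusion.** The point holds as one of alignment and efficiency, not of invalidity. The stated analysis is not fixed to the 6-month change: it does not say clearly which test decides, the interaction can be significant from a month-3 effect alone, and baseline HbA1c is a covariate in neither analysis.

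Under the stated assumptions (SD 1 as the SD of values, 62 per arm, r = 0.3/0.5/0.7), the size is:
- a month-3-only effect makes the interaction significant in 67%/82%/97% of trials if it is 0.5%, and 21%/28%/44% if it is 0.25%;
- for a 0.5% effect at month 6, adjustment raises power from 79% to 82%/89%/97%;
- interaction power for that effect is 54%/70%/90% if it builds gradually and 67%/82%/97% if it is already full at month 3;
- the null rejection rate is about 9–10% only if either test could decide, which the text leaves open but does not state.

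It does not follow that the trial is too small or its tests biased. Lack of adjustment costs precision and leaves chance imbalance uncorrected, but it does not bias the comparison on average. The planned 126 is enough for the adjusted analysis across this range.

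**What to change.** Name one primary estimate: the between-group difference in HbA1c at 6 months, adjusted for baseline HbA1c, with its 95% CI. It can come from ANCOVA, or from the 6-month contrast of a linear mixed model of the month 3 and month 6 values with baseline HbA1c, group, visit and group-by-visit. State that this result decides. Make the month-3 contrast and the overall group-by-time interaction supportive, and do not let a Mann–Whitney test replace the primary mean-difference estimate. Add the 6-month time point to the Study outcomes section so that it matches the Background.

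The cost is wording only: the visits, data, software (SPSS) and sample size are unchanged. The change should be made before outcome data are seen, because it settles which result is the trial's answer.

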### Data collection

Participants' baseline data will be collected three days before discharge, and a questionnaire regarding demographics will be completed. Data collection will be conducted at 3 and 6 months after discharge. Patients will attend clinical appointments in the study hospital or designated community hospitals to complete clinical and laboratory assessments. Research assistants will upload the results to the diabetes management platform for secure collection. The research assistant will collect the questionnaires face-to-face during the outpatient visit. The patients' blood glucose data and hypoglycemia events will be supervised and consulted by CNs through the app or telephone. Readmission will be determined by referring to the participant's medical history in the general hospital. All data will be double-entered and checked for consistency. The study flowchart and participant data collection are depicted in Fig. 1 and Table 1.

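### The missing-data rule credits imputation to ITT, which is not an imputation method; without a real one, the repeated-measures ANOVA excludes anyone who misses a visit and is not ITT

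*Protocol article*

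**What the plan says.** All statements are in the protocol article.

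- **Analysis set (Statistical analysis).** The analysis is to follow intention-to-treat, "meaning that all eligible patient information was included in the analysis regardless of whether the intervention was completed".
- **Missing data (Statistical analysis).** The only rule is "The ITT analyses will also be used to impute missing study data".
- **Model for change over time (Statistical analysis).** Differential change between groups "will be assessed by repeated-measures ANOVA", with a group-by-time interaction over baseline, 3 months and 6 months, to judge the effect on the primary outcome. The software is SPSS 23.0; no procedure within it is named.
- **Other comparison (Statistical analysis).** Under the label of the primary analysis, the section also lists t-tests or Mann–Whitney tests between groups at baseline and endpoint.
- **Primary outcome (end of Background).** Change in HbA1c at the 6-month follow-up.
- **Visits (Data collection).** "Data collection will be conducted at 3 and 6 months after discharge".
- **Expected loss (Sample size).** "Allowing for a 10% attrition rate", 126 participants become 138, or 69 per arm.

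**The concern.** An ITT analysis is defined by its participants and by their assignment to arms. It does not say what value a missing HbA1c should take, under what model, or under what assumption about why it is missing. The sentence therefore commits to imputation but points to something that cannot impute.

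This matters because of the model beside it. Classical repeated-measures ANOVA works on complete rows. A participant with baseline and month 3 but no month 6 drops out of the analysis, and so does one with baseline and month 6 but no month 3. If the analyst finds no usable rule and runs the ANOVA on the data as they stand, the ITT promise in the same paragraph is broken and observed HbA1c values are thrown away.

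The exclusions may not be neutral. Participants are unblinded, and the intervention includes app reminders before follow-up that are not described for the control arm (Study intervention). Who attends may therefore differ between arms. If the rule is left open, the missing-data method may also be chosen after the data have been seen.

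**Working it through.** **1. The statements side by side**

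| Element | What it needs or does | Consistent with ITT as defined? |
|---|---|---|
| ITT definition | Everyone stays in, whether or not the intervention was completed | – |
| Imputation sentence | Intends imputation; names ITT as the means | Right intention, no means |
| Repeated-measures ANOVA, 3 time points | All three HbA1c values per participant | Only if missing values are really filled in |
| Endpoint t-test | Month-6 value only | Loses those without month 6; keeps those who missed only month 3 |

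**2. The plan's own sample size**

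Inputs (Sample size): difference 0.5, SD 1, power 0.80, two-sided alpha 0.05.

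n per arm = 2 × (1.960 + 0.842)² × 1² / 0.5² = 62.8, rounded up to 63, so 126 in total. This matches the plan. For attrition, 126 × 1.10 = 138.6 and 126 / 0.90 = 140; the stated 138 is close to both.

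**3. Power if incomplete participants were deleted**

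Power = Φ(0.5 × √(n/2) − 1.960), with n per arm = 69 × (1 − loss). This is the same two-group calculation that the plan uses, not a calculation for the interaction test.

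| Share missing any HbA1c value | Total analysed | Power |
|---|---|---|
| 0% | 138 | 0.836 |
| 10% (the plan's attrition) | 124 | 0.796 |
| 15% (assumption) | 117 | 0.773 |
| 19% (assumption: 10% missed independently at each follow-up visit, 1 − 0.9²) | 112 | 0.753 |
| 20% (assumption) | 110 | 0.748 |

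At the planned loss, power is the design value to within rounding. The lower rows need more loss than the plan foresees.

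**4. Illustration of selective exclusion**

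None of the inputs to this step comes from the protocol. Assumptions: no true effect; SD 1 at each visit; correlation 0.5 between baseline and each follow-up visit and 0.6 between months 3 and 6. In the intervention arm, those with the worst month-3 HbA1c leave before month 6. In the control arm, the same share is lost at random.

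Simulated bias in the complete-case contrast for change from baseline to month 6, in favour of the intervention:

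- 10% loss: about 0.02 HbA1c points
- 20% loss: about 0.04 HbA1c points

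Closed-form check: removing the top share f of a standard normal variable shifts the mean of the rest by φ(z)/(1 − f), where z is the cut-off. The shift passes to the change score in proportion to the difference in correlations, 0.6 − 0.5 = 0.1.

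- f = 10%: 0.1 × 0.1755/0.90 = 0.020
- f = 20%: 0.1 × 0.2800/0.80 = 0.035

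The two agree within simulation error. The bias is small here because the two correlations nearly cancel; a stronger mechanism could give more. In this scenario the month-3 values that drive the dropout were observed. The ANOVA discards them, whereas a likelihood-based model would use them.

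**The case against.** The strongest defence is that the plan does say missing data will be imputed. A repeated-measures ANOVA on properly imputed data would keep all 138 participants. A reader might infer that the primary analysis simply becomes a complete-case analysis. The article does not support that: it nowhere says that participants with a missed visit will be excluded, and deletion follows only if no real imputation is done. This part of the defence stands.

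A second defence is that the article is condensed and the imputation method may be set out in a full protocol or SAP that is not shown. The absence of imputation detail is indeed no finding. What remains is an error in what is stated: ITT is named as the means of imputation, and no further detail makes that sentence correct.

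Third, a reader might say that someone seen at baseline and month 6 but not at month 3 would be lost although the primary outcome was observed. That is true of the ANOVA without imputation. It is not true of the endpoint comparison, which the section also places under the primary analysis.

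Fourth, a reader might infer a material loss of power, to about 75–77%. That needs a further 5–10% of participants to miss month 3 on top of the planned 10%, and nothing in the article supports such a figure. It would also carry the ANOVA's deletions into a power formula for a two-group comparison. The power argument is therefore not made.

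Finally, loss that depends on arm alone would not bias the comparison, and the illustrated bias of 0.02–0.04 is small against the 0.5 target. Both points stand and limit the size of the concern.

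**Conclusion.** The concern holds in a limited form. The missing-data sentence cannot be carried out, because ITT is an analysis principle. Unless a real method is used, the repeated-measures ANOVA will omit anyone without all three HbA1c values and will not meet the section's own ITT definition.

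The plan does not commit to a complete-case analysis, and the power cost at the planned attrition is negligible. What is at stake is selective exclusion and wasted HbA1c data. The size of any bias cannot be fixed from the article, since it depends on who is missing and why. The illustration is small but rests entirely on assumed correlations and an assumed dropout pattern.

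The conclusion also rests on the ANOVA being run in its classical form, which the article's wording suggests but which it does not tie to a particular SPSS procedure. This should be corrected before any outcome data are compared by arm.

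**What to change.** 1. Delete the sentence that assigns imputation to ITT. State ITT separately as all randomised participants, analysed in the arm to which they were allocated.
2. Replace the repeated-measures ANOVA with a likelihood-based mixed model for repeated measures. The outcomes are every observed HbA1c value at months 3 and 6; the terms are group, visit, group-by-visit and baseline HbA1c as covariate. Name the 6-month between-group difference as the primary contrast. The model is valid if data are missing at random, and it keeps a participant who has either follow-up value.
3. Add a sensitivity analysis by multiple imputation within arm, with a delta shift to represent data missing not at random. This also brings in participants with no post-baseline value, who add nothing to the mixed model's treatment contrast.

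SPSS 23 can fit the mixed model and run multiple imputation. Visits and sample size do not change. The cost is a revised paragraph and modest extra analysis work.
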